## Abstract

**Background:**

Persons with diabetes have 27% elevated risk of developing colorectal cancer (CRC) and are disproportionately from priority health disparities populations. Federally qualified health centers (FQHCs) struggle to implement CRC screening programs for average risk patients. Strategies to effectively prioritize and optimize CRC screening for patients with diabetes in the primary care safety-net are needed.

**Methods:**

Guided by the Exploration, Preparation, Implementation and Sustainment Framework, we conducted a stakeholder-engaged process to identify multi-level change objectives for implementing optimized CRC screening for patients with diabetes in FQHCs. To identify change objectives, an implementation planning group of stakeholders from FQHCs, safety-net screening programs, and policy implementers were assembled and met over a 7-month period. Depth interviews (*n* = 18–20) with key implementation actors were conducted to identify and refine the materials, methods and strategies needed to support an implementation plan across different FQHC contexts. The planning group endorsed the following multi-component implementation strategies: identifying clinic champions, development/distribution of patient educational materials, developing and implementing quality monitoring systems, and convening clinical meetings. To support clinic champions during the initial implementation phase, two learning collaboratives and bi-weekly virtual facilitation will be provided. In single group, hybrid type 2 effectiveness-implementation trial, we will implement and evaluate these strategies in a in six safety net clinics (*n* = 30 patients with diabetes per site). The primary clinical outcomes are: (1) clinic-level colonoscopy uptake and (2) overall CRC screening rates for patients with diabetes assessed at baseline and 12-months post-implementation. Implementation outcomes include provider and staff fidelity to the implementation plan, patient acceptability, and feasibility will be assessed at baseline and 12-months post-implementation.

**Discussion:**

Study findings are poised to inform development of evidence-based implementation strategies to be tested for scalability and sustainability in a future hybrid 2 effectiveness-implementation clinical trial. The research protocol can be adapted as a model to investigate the development of targeted cancer prevention strategies in additional chronically ill priority populations.

**Trial registration:**

This study was registered in ClinicalTrials.gov (NCT05785780) on March 27, 2023 (last updated October 21, 2023).

**Supplementary Information:**

The online version contains supplementary material available at 10.1186/s12875-024-02496-0.

## Background

Patients with diabetes mellitus have an estimated 27% elevated lifetime risk of developing colorectal cancer (CRC), and are disproportionately from priority health disparities populations (e.g., low-income, Non-Hispanic Black and Hispanic) [1, 2]. Nationally, guideline concordant receipt of CRC screening for patients with diabetes is not significantly different for women with diabetes (57% vs. patients without diabetes 58%) and is significantly higher among men with diabetes (63% vs. patients with diabetes 58%) [3]. CRC screening for patients with diabetes, who do not have other indications of high risk (e.g., family history of CRC, polyp removal during colonoscopy, personal history of CRC, inflammatory bowel disease) are advised to follow the average risk screening recommendations [4]. Federally qualified health centers (FQHCs) primarily serve as primary care for priority health disparities populations and struggle to sustainably implement CRC screening programs for average-risk patients which includes patients with diabetes. CRC screening uptake in FQHCs populations has been consistently lower (44.1%) than the national average for average risk, age-eligible adults (67.3%) [5].

Persons receiving diabetes care in FQHCs have elevated health risks overall and higher rates of poverty and low-income status than the general population [6]. Ten percent of FQHC patients have a diabetes diagnosis and more than a third within this group have uncontrolled diabetes (HbA1c > 9%). Failure to implement preventive CRC screenings translates to an average of 6.5 years of lost life for patients subsequently diagnosed with CRC [7]. Moreover, this contributes to greater burden for patients with diabetes who are diagnosed with CRC who suffer greater morbidity, all-cause mortality, and cancer-specific mortality compared to CRC patients [8–10]. Therefore, efforts to prioritize CRC screening for patients with diabetes are needed in primary care safety-net settings.

Multiple evidence-based CRC screening tests are available which complicates implementation. The U.S. Preventive Services Taskforce (USPSTF) recommends CRC screening in adults aged 45–75, with multiple screening options available including non-invasive stool based testing: high sensitivity guaiac fecal occult blood tests (gFOBT), fecal immunochemical test (FIT), FIT plus stool DNA testing (FIT-DNA); and direct visualization tests: colonoscopy, computed tomography (CT) colography, and flexible sigmoidoscopy (FS) (with or without FIT) (see Table 1 for intervals) [4]. Colonoscopy and FS, have been shown to reduce mortality by (68% and 28%, respectively). FIT and FOBT are associated with 13–33% mortality reductions. Stool-based testing mortality reductions require sustained annual adherence. [11–14]. Research has shown that failures to screen at all, to screen at appropriate intervals, and to follow-up on abnormal results are associated with risk of CRC death [15].

**Table 1 Tab1:** Evidence-based CRC tests & testing intervals

Test	Testing Intervals
**Stool-based tests**	
gFOBT	Annual
FIT	Annual
FIT-DNA	1–3 yrs.
**Direct visualization tests**	
Colonoscopy	10 yrs.
CT colonography	5 yrs.
FS	5 yrs.
FS with FIT	10 year/annual

Given major differences in mortality reduction benefits, temporal intervals for retesting, costs, and patient burden, controversies have emerged surrounding the pros and cons of testing methods [16, 17]. Colonoscopy and FS allow for polypectomies, which can prevent CRC [18, 19]; however, FS is not widely used in the U.S, because colonoscopy evaluates the entire colon, can be done every 10 years, and is associated with a greater mortality reduction [20]. A re-analysis of the USPSTF data suggest that prevention, through the removal of polyps during colonoscopy, is the sole mechanism of CRC mortality reductions [19]. Colonoscopy is thus the “gold standard,” despite critiques about the rigor of this evidence (e.g., indirect and observational). [21–24]. In FQHCs, non-invasive tests are emphasized and colonoscopies are often a second line-screening based on abnormal gFOBT/FIT findings. [25]. Non-invasive tests are emphasized because these are less costly, require less time (and time off of work), less complicated to complete, do not require transportation, and are guideline concordant [26]. Despite stool based testing’s acceptability, US-based trials in FQHCs designed to increase annual adherence to stool-based testing have reported low screening adherence over three years (10.4–16.4%) [27–29].

Prioritizing colonoscopy with longer testing intervals in under-resourced FQHCs for patients with diabetes introduces fewer opportunities for care breakdowns, is guideline concordant, and prevents CRC by removing premalignant colonic polyps. Guided by the Exploration, Preparation, Implementation and Sustainment [30]. (EPIS) framework, this research study will develop and evaluate targeted CRCs screening strategies for patients with diabetes in safety-net settings. This study addresses known implementation challenges using a “designing for dissemination” approach [31–33] that attends to important contextual, organizational capacity and patient complexity factors that impact CRC screening program implementation in clinics and uptake among patients with diabetes.

### Conceptual framework

The design of this study was guided by the EPIS framework. EPIS is an evidence-based practice (EBP) implementation framework that includes four defined phases for assessment of inner and outer contextual factors that influence EBP implementation (see Table 2). For this study, the EBP is CRC screening uptake among age eligible patients with diabetes. Exploration is the act of identifying patient needs and the availability of EBPs to address identified needs, and the decision to adopt evidence into practice based on fit within the inner clinical context. During this phase, the adaptations to the evidence are based on system, organization, and individual patient factors. Preparation includes planning implementation, inventorying proposed challenges, and developing strategies to overcome anticipated barriers. A critical component of this phase is the planning of implementation strategies to support EBP utilization in the next two phases and to address organizational climate to ensure that EBPs will be supported, expected, and rewarded. During the clinical trial, this study focuses on implementation, the process of assuring and balancing fidelity to the EBP delivered with adaptations needed to assure program success. Sustainment focuses on maintenance and program and factors impacting implementation over the long haul. EPIS considers innovation factors, which are the characteristics of the EBP being implemented. The innovation-EBP fit considers if the EBP fits the patient, provider, and organizational needs. Innovation factors are assessed and can be adapted to maximize the fit of an EBP while maintaining the core elements of the intervention to retain fidelity.

**Table 2 Tab2:** EPIS constructs for implementation of SURE: CRC4D toolkit to promote screening in patients with diabetes

Domains	Inner context	Outer context
Actors	Decision makers, Champions, Adopters, Staff	Patients, Policymakers/Advocates, Funders
Resources	Electronic Health Record, Materials, Supports	Referral for CRC screen; Patient Navigation; Community Organizations
EBP	Core elements for fidelity; EBP fit with Organization	EBP fit with practice; Practice Incentives

Acronyms: EBP: evidence-based practice, CRC: colorectal cancer screening

## Methods and design

### Identifying multi-level change levers: a multi-method stakeholder informed approach

Earlier phases of this research focused on the Exploration and Preparation phases, while the current protocol describes the intervention implementation and its evaluation. During the exploration phase, a secondary analysis was conducted of a nationally representative data set to identify patient level determinants of CRC screening uptake overall (i.e., with any test) and test-specific uptake among individuals with diabetes. We explored disparities in uptake overall and testing type based on race, ethnicity, income, and educational status. Additionally, a scoping literature review was performed to identify evidence-based interventions and implementation strategies for CRC screening and diabetes management in FQHCs. Based on this scoping review, we identified additional interventions and implementation strategies, using the Expert Recommendations for Implementing Change (ERIC) taxonomy [34]. A list of interventions and implementation strategies was compiled related to diabetes management processes to expand an existing measure that was developed and used to evaluate the use of evidence-based intervention and implementation for CRC in FQHCs [35].

For the preparation phase of the formative research, we used implementation mapping, an iterative process that incorporates community based participatory research principles [36, 37]. An Implementation Planning Group (IPG) was assembled to represent a diversity of implementation actors (e.g., clinicians, state-level decision makers, screening safety-net programs) who work in and with FQHCs. The goal of the IPG, which met 5 times over a six-month period, was to develop shared understandings of the research problem based on empirical knowledge from the national survey analysis, the scoping review of the literature, and local knowledge of the IPG members about patient population and clinic system capacities. The IPG group identified and prioritized the selection of implementation strategies to improve CRC screening uptake for patients with diabetes. The IPG and research team iterated an implementation plan specifying multi-level change objectives and implementation determinants to develop supports to help prioritize CRC screening implementation for patients with diabetes.

Guided by the insights of the exploration and preparation phases, we developed the Strategic Use of Resources for Enhanced ColoRectal Cancer Screening in Patients with Diabetes (SURE: CRC4D) implementation toolkit, which includes tailorable materials and protocols that will be tested in a single arm, hybrid type 2 effectiveness-implementation single arm clinical trial. The objectives of this trial are to:

Determine the effectiveness of the SURE: CRC4D multi-component implementation strategies to increase CRC screening uptake among patients with diabetes.Evaluate the fidelity, feasibility, and acceptability of SURE: CRC4D implementation.Refine the SURE: CRC4D toolkit based on multi-level user feedback and conduct an evaluation to promote scalability and sustainable use.

### Methods

#### Study participants and setting

This single arm trial will be conducted in six FQHC clinical sites in New Jersey. Eligibility criteria for the FQHC clinics include: (1) provide care to at least 450 patients aged 50–74 years; (2) 10% of patient population previously diagnosed with diabetes; (3) located in New Jersey; and, 3) clinical and administrative leadership willing to engage in the intervention and research requirements (interviews, data validation, process evaluation). Implementation outcomes will be assessed using mixed methods guided by the EPIS constructs (see Table 2). The methods of this study have been reported using Standard Protocol Items: Recommendation for Interventional Trials (SPIRIT) guidelines (Supplemental file 1).

During the implementation a clinic-based registry of patients eligible for CRC screening will be developed for each clinic at baseline and updated at six and 12 months post-baseline. Patient eligibility criteria will include: (1) patients not up-to-date or due for CRC screening [4]. based on electronic health record (EHR) documentation (e.g. FOBT/FIT test in last year, flexible sigmoidoscopy within 4 years, or colonoscopy within 9 years), (2) previous diagnosis of type II diabetes, (3) age-eligible for CRC screening (45–74 years of age) and (4) ) FIT/FOBT that has been ordered for more than 6 months that has not been completed or a sigmoidoscopy or colonoscopy referral that has not been completed for 12 or more months. Patients are excluded if they have EHR documentation medical conditions not concordant with standard CRC screening intervals (e.g. prior CRC diagnosis, inflammatory bowel disease, renal failure, etc.) [4].

The NJ Primary Care Research Network (NJPCRN) will recruit eligible clinics for participation. The NJPCRN is an Agency for Healthcare Research and Quality recognized practice-based research in primary care practices. The NJPRN will contact FQHCs that participated in previous research and ask IPG members to make introductions with their FQHC leadership networks. Emails with study flyers will be sent to the FQHC with follow-up telephone outreach. This protocol has been approved by the Rutgers University Institutional Review Board (Pro2020002075). All study participants will be asked to provide informed consent prior to participation in all phase of this research. We expect the distribution of patient participants to reflect the racial/ethnic diversity of the FQHCs recruited, who predominantly serve low-income, racial, and ethnic minority populations.

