### Quantitative analysis

Descriptive statistics will be used to summarize patient and clinic characteristics. We will declare our intervention a success if at least 25% of those unscreened are screened at 12-month follow-up in this difficult to reach population. We will declare the optimization of screening a success if 15% of those unscreened are screened with a colonoscopy or flexible sigmoidoscopy at 12-months. Overall improvement metrics are comparable to improvements in previous CRC screening implementation studies in FQHCs [65, 66]. At baseline, we will calculate average screening rates and their confidence intervals across all practice sites in intent to treat analyses and at 12-months we will assess screening rates and their confidence intervals for all sites. The confidence intervals will be compared to 25%. We will compare differences in CRC screening by glucose control, sex, and race/ethnicity.

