### Power calculations

The value of information method [67] was utilized to select a sample size balancing the costs and feasibility goals of the trial. This sample size (e.g., six clinic sites, assuming at least *n* = 30 patient in each) is sufficient to generate preliminary estimates of the estimated effect (80% confidence interval) of the implementation strategy on CRC screeningrates [68, 69]. In developing the power calculation, we assume equal numbers of patients (*n* = 50) per clinic (the anticipated number of eligible patients, *n* = 450 CRC screening eligible, with > 10% diabetes diagnosis). Of those with diabetes, we expect 40% to be up-to-date with screening guidelines based on the average rate of CRC screening in FQHCs [70]. Thus, the target sample size is *n* = 30 patients in each FQHC.

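### Read literally, patient criterion (4) admits only patients with an old uncompleted order or referral, but the target of 30 per clinic makes no allowance for it

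*Protocol article*

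**What the plan says.** Under the heading Study participants and setting, the registry admits patients by four numbered criteria. The first is broad: "1) patients not up-to-date or due for CRC screening [4]. based on electronic health record (EHR) documentation". The second is a diagnosis of type II diabetes. The third and fourth are joined by an and: "3) age-eligible for CRC screening (45–74 years of age) and (4) ) FIT/FOBT that has been ordered for more than 6 months". The fourth reads "FIT/FOBT that has been ordered for more than 6 months that has not been completed or a sigmoidoscopy or colonoscopy referral", and its second limb carries its own time limit: "a sigmoidoscopy or colonoscopy referral that has not been completed for 12 or more months".

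Under Power calculations, the starting figure is 50 patients with diabetes: "we assume equal numbers of patients (*n* = 50) per clinic". It is tied to "450 CRC screening eligible, with > 10% diabetes diagnosis". One reduction follows: "Of those with diabetes, we expect 40% to be up-to-date with screening guidelines based on the average rate of CRC screening in FQHCs". The target is then 30 per clinic.

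Under Quantitative analysis, the intervention succeeds if "at least 25% of those unscreened are screened at 12-month follow-up". A second rule sets 15% of the unscreened for colonoscopy or flexible sigmoidoscopy. The trial objectives and the primary outcome definition refer to patients with diabetes and mention no outstanding order or referral. Table 4 divides both primary measures by the patients eligible.

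**The concern.** With an and before (4), a patient must be overdue and must also hold a stool-test order or endoscopy referral that has gone uncompleted for the stated time. A patient who is overdue because nobody ordered a test fails (4) and never enters the registry. The sample-size section describes a wider group: everyone with diabetes who is not up to date.

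The difference matters because eligibility sets the denominator of both primary measures in Table 4, and of the fidelity measure under Process data outcomes. If (4) is applied literally, the trial estimates conversion among known non-completers. Such patients may respond differently from patients never offered a test, and a single-arm design has no control group against which that difference would cancel. Clinics also have different electronic records. If one site reads (4) as a requirement and another as a clarification, their rates will not be comparable.

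**Working it through.** **Inputs from the article**
- Patients with diabetes per clinic: 50 (Power calculations)
- Share up to date: 40% (Power calculations)
- Clinics: 6 (Study participants and setting)
- Success level for any screening: 25% (Quantitative analysis)
- Planned interval: 80% confidence (Power calculations)

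**Input not in the article**
- f, the share of not-up-to-date patients who also meet (4). I use 30–60% as an illustrative assumption.

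**Step 1. Reproduce the plan's figure.**
50 × (1 − 0.40) = 30 per clinic, and 6 × 30 = 180. The target is reproduced exactly. The 50 needs 50/450 = 11.1% with diabetes, which agrees with the stated share of more than 10%. The only reduction is for being up to date.

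**Step 2. Apply criterion (4) as written.**
n per clinic = 50 × 0.60 × f = 30 × f. This equals 30 only if f = 100%.
- f = 0.30: 30 × 0.30 = 9 per clinic, 6 × 9 = 54 in total
- f = 0.60: 30 × 0.60 = 18 per clinic, 6 × 18 = 108 in total

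**Step 3. Precision at a 25% rate.**
Half-width = 1.2816 × √(0.25 × 0.75 / N), ignoring clustering.
- N = 180: 1.2816 × √(0.1875/180) = 0.0414, or 4.1 points
- N = 108: 1.2816 × √(0.1875/108) = 0.0534, or 5.3 points
- N = 54: 1.2816 × √(0.1875/54) = 0.0755, or about 7.6 points

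**Step 4. Clinic size needed to keep 30 under the literal criteria.**
Patients with diabetes needed = 30 / (0.60 × f).
- f = 0.60: 30/0.36 = 83.3, so 84; at 11.1% with diabetes, about 83.3 × 9 = 750 screening-eligible patients
- f = 0.30: 30/0.18 = 166.7, so 167; about 166.7 × 9 = 1,500 screening-eligible patients

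The planning figure is 450.

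**Step 5. Compare the populations.**
- Eligibility, read literally: not up to date, with diabetes, of eligible age, and holding an old uncompleted order or referral
- Sample-size base: with diabetes and not up to date
- Success rules: the unscreened, with no order condition stated
- Objectives and primary outcome: patients with diabetes, with no order condition stated

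The first and second lines conflict directly. The third and fourth lie closer to the second but are less specific.

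**The case against.** The strongest reply is that this is loose drafting. The clinic criteria in the same section use the number 3 twice, criterion (1) illustrates being overdue with examples of being up to date, and (4) has a stray parenthesis and describes an order where a patient attribute is expected. Criterion (4) may only have been meant to say that a stale order does not count as screening. That is plausible, but the article does not say so, and a registry query would be built from the text. The inconsistency therefore stands, while a claim that the restriction is deliberate does not.

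A reader might infer three stronger things that the documents do not support.
- That the trial will fall short of 30 per clinic. The share f is not given, 450 patients is a minimum for clinic entry, and actual clinic sizes are unknown. The sample was also chosen by a value-of-information method for preliminary estimates, which a moderately wider interval would not defeat.
- That the success rules flatly contradict eligibility. The unscreened may mean the unscreened within the registry. That conflict is softer than the one with the sample size.
- That patients with no order are a main target of the strategy. The description of audit and feedback does not single them out.

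**Conclusion.** The point holds as an inconsistency between eligibility and sample size. As written, (4) is an added requirement, and 30 per clinic follows from the stated inputs only if every patient not up to date meets it. This part is exact and needs no assumption.

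The size of the effect is conditional. With f at 30–60%, and clinics no larger than assumed, the plan yields 54–108 patients instead of 180, and a half-width of about 5.3–7.6 points instead of 4.1, before clustering. A different f or larger clinics would change these figures. Because eligibility is the denominator of both primary measures, the wording should be settled whichever reading was meant.

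**What to change.** Before the baseline registries are built, reconcile the patient criteria, the primary outcome definition, the success rules and the power calculation so that all describe one population.

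- **Least change.** Make eligibility (1) + (2) + (3), and reword (4) as a clarification under (1): an old uncompleted order or referral does not count as screened. This fits the objectives, primary outcome, success rules and sample size. State also how patients with a recent, still-pending order are handled. If they are admitted, tests ordered before the programme could count toward the 25%.
- **If the restriction to non-completers is intended.** Keep (4), restate the target number with a justified value of f, and name non-completers as the population of the success rules.
- **If results are to be shown by prior-order status.** Collect both the baseline denominators and the 12-month numerators by that status. Patient data are aggregate, so a baseline count alone would not allow it.

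The cost is a short text amendment and one common registry query. Under the first option the registry is larger than under the literal reading (180 against 54–108 on the assumption above), but 180 is the number already planned. Reporting by prior-order status adds a few aggregate counts per clinic.
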